### Data management

Data are collected on paper forms by CHWs and other field workers during home visits with enrolled mothers and their newborn babies. Forms are checked for accuracy and completeness by field supervisors prior to transport for data entry in Dhaka. A data entry prioritization protocol enables time-sensitive data, such as results from screening tests or treatment follow up data, to be entered locally at the field site/laboratory; this enables minimal turn-around time between screening and treatment, and allows real-time assessment of compliance and monitoring of treatment-related adverse events. All forms are eventually entered into a secure Oracle database using customized data entry screens, with built-in range and validation checks. The database is backed up daily and a de-identified version is transferred (using encrypted peer-to-peer transfer software) on a regular basis to Baltimore, USA for archiving and creation of merged analytic files.

### Analysis

Interim (i.e. for DSMB analyses) and final analyses will follow the same protocol. First, we will present descriptive information on the recruitment, enrollment, and follow up of women and their newborns (i.e. a participant flowchart). We will then assess characteristics of the enrolled pregnancies to determine the extent to which our randomization procedure achieved comparability; these characteristics will include maternal, paternal, household, and socio-economic variables. For clusters allocated to the intervention arm we will describe the coverage of the screening and treatment intervention, including the distribution of time (i.e. gestational age) at screening, results of the initial and follow up vaginal swab (overall AVF, and intermediate vs. bacterial vaginosis) and urine tests (normal, intermediate asymptomatic, intermediate symptomatic, and high-burden single growth), and compliance with treatment. For the 10 % sub-sample of women in the control clusters who are randomly selected for the screening and treatment intervention, we will generate a similar set of intervention/coverage related indicators and compare these with those of the larger group of women in the intervention clusters.

The next stage of analysis will focus on describing the impact of the intervention on the primary and secondary outcomes. The gestational age at birth will be defined for each pregnancy as the number of days between last menstrual period (reported and recorded at enrollment) and the date of the pregnancy outcome. The primary study endpoint is preterm live birth, and thus we will present, in each group, the number of live births born prior to the pregnancy reaching 37 complete weeks (numerator) and the total number of live births (denominator). The preterm “rate” will be estimated as this proportion with a 95 % binomial exact confidence interval. The impact of the intervention will be assessed by estimating the relative risk of preterm live birth and the absolute risk difference using binomial regression models with a log and identity link functions, respectively. The standard error of this estimate will be constructed using generalized estimating equations and a 95 % confidence interval calculated. We will follow a similar analytic approach to estimate live births prior to 34 weeks (by group and with relative risk) and to estimate the average gestational age at birth for live births, for which we will use a linear regression model with an identity link function and GEE to estimate errors.

We will then expand the pool of analyzable pregnancies to include all spontaneous delivery (i.e. late miscarriages and stillbirths, in addition to live births) and follow an identical approach to estimate the impact of the intervention on this broader set of pregnancies. We will estimate stillbirth and neonatal mortality rates (very early: <1 day, early: <7 days, and overall neonatal mortality: <28 days), and compare across the groups using binomial regression models. Other secondary outcomes of interest that will be compared across the groups include early-onset neonatal infection (defined through use of a sign-based algorithm and restricted to the first 7 days of life) and maternal report of infection in the first 7 and 28 days after delivery.

These models will be presented without adjustment, and a second set of analyses will be conducted with adjustment for any variables found to be imbalanced between the groups (if necessary). Planned sub-analyses to examine for effect modification include stratifications by age at delivery and parity. All estimates of the intervention's impact will be presented with confidence intervals constructed from standard error estimates adjusted for the cluster randomization using GEE.

Additional planned analyses that are not related directly to the impact of the intervention include descriptive analyses of the organisms isolated from urine specimens, antibiotic resistance patterns, contamination rates over time, and adverse event reporting.

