### Randomization

The units of randomization in this trial are the 24 CHW areas, each comprising several adjacent villages. Allocation to the intervention vs. control arms was done via a restricted randomization procedure. All $$ \left(\begin{array}{c}\hfill 24\hfill \\ {}\hfill 12\hfill \end{array}\right) $$ possible randomization sequences were generated where each sequence allocated 12 of the CHW areas to either intervention or control. Using data on births and preterm status from our prior study in this area [42], we restricted the set of eligible sequences to those where intervention vs. control ratios of predicted preterm birth and predicted total births were within 0.975 to 1.025. An additional criterion for retaining a sequence as eligible was that the 13 CHW areas that had participated in a prior study on birth spacing (“The Health Fertility Study”) were allocated equally to intervention and control (i.e. 6 and 7 or 7 and 6). Among the 2,704,156 sequences, 164 sequences met the criteria, from which a single sequence was randomly selected. Workers and participants in the study are not blinded to the intervention group but are not aware of the study aims/hypotheses.

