Having selected an effect size of 18.4 % (i.e. relative reduction in the population rate) we proceeded to estimate the sample size required. As the number of clusters available is fixed (*n* = 24), we followed an approach where first the sample size required under a naïve assumption of individual randomization was calculated, and then inflated by a factor (“design effect”) in order to account for correlation within CHW areas arising from the cluster-randomized design. We estimated this design effect as (1+ ***ρ*** •[ ***θ*** -1+ ***θ γ***^2^]), where ***ρ*** is the estimated intra-cluster correlation coefficient, ***θ*** is the mean sample size per cluster under individual randomization, and ***γ*** is the coefficient of variation in the cluster size [59]. Among ~16,000 births between June 2007 and September 2008 in this trial area, the intra-cluster correlation coefficient in this setting was 0.0060 (95 % CI: 0.0025–0.0095) and the coefficient of variation in cluster size was 0.33, leading to a design effect of 1.95 for preterm live birth. Taking this design effect into account, the number of live births required in each group to observe the estimated 18.4 % relative reduction with 80 % power and allowing 5 % Type I error is approximately 3367. Finally, we assumed that 90 % of the women screened at 13–19 weeks would have a live birth and 10 % would be lost to follow up, requiring enrollment of a total of 8314 in both control and intervention areas at the 13–19 week visit. Given a total population size of ~100,000 and a crude birth rate of 27/1000, we project that this sample will be reached in approximately 37 months, with total field work and follow-up of about 4 years.

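### The 95% interval planned for each arm's preterm rate ignores clustering and is too narrow if the areas are read as a sample

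*Protocol article*

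**What the plan says.** For the primary endpoint the Analysis section presents, in each group, the count of preterm live births over all live births, and then fixes the interval: the rate is to be "estimated as this proportion with a 95 % binomial exact confidence interval". The relative risk and risk difference follow, with standard errors from generalized estimating equations. A later paragraph of that section sets the general rule: "All estimates of the intervention's impact will be presented with confidence intervals constructed from standard error estimates adjusted for the cluster randomization using GEE". An arm's own rate is not an estimate of impact, so neither the GEE sentence nor the general rule reaches it.

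The Randomization section describes an allocation in which "each sequence allocated 12 of the CHW areas to either intervention or control". The section Sample size and analysis states that, in about 16,000 earlier births in the area, "the intra-cluster correlation coefficient in this setting was 0.0060 (95 % CI: 0.0025–0.0095"), and that "the coefficient of variation in cluster size was 0.33, leading to a design effect of 1.95 for preterm live birth".

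**The concern.** The exact binomial interval is correct when births are independent. Here the plan has measured within-area correlation for this same outcome, with a confidence interval that excludes zero, and has inflated the sample for it. It then prescribes an interval that sets the correlation to zero. This is a method the document states, not a detail left for a later plan.

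What is at stake is the precision shown for the two arm rates. Intervals that are too narrow overstate how well each rate is known. They may also sit in the same table as a clustered relative risk that appears to disagree with them. Since the Analysis section applies the same protocol to interim and final analyses, the format would also reach the monitoring board.

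**Working it through.** **Inputs.** From Sample size and analysis: ICC ρ = 0.0060 (0.0025 to 0.0095); cluster-size CV γ = 0.33; preterm rate 20%; relative reduction 18.4%, so 16.32% under intervention; 80% power; 5% type I error, taken as two-sided; 3367 live births per arm. From Randomization: 12 areas per arm.

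**Step 1: reproduce the plan's figures.** For two proportions under individual randomization,

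n = [1.96·√(2·0.1816·0.8184) + 0.8416·√(0.20·0.80 + 0.1632·0.8368)]² / 0.0368² = 1722 per arm.

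The plan's design effect is 1 + ρ(θ − 1 + θγ²), with θ the mean cluster size under individual randomization. Here θ = 1722/12 = 143.5, so

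DE = 1 + 0.006·(143.5 − 1 + 143.5·0.1089) = 1.949, against 1.95 printed.

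1722 × 1.949 = 3356, against 3367 printed. The inputs and formula are therefore read correctly.

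**Step 2: design effect at the planned cluster size.** The interval will be computed on the inflated sample, where the mean cluster size is 3367/12 = 280.6. The same formula gives

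DE = 1 + 0.006·(280.6 − 1 + 280.6·0.1089) = 2.86.

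**Step 3: half-widths at a 20% rate.**
- Exact binomial for 673/3367: 18.65% to 21.38%, half-width 1.37 points.
- Clustered, normal: 1.96·√(0.16/3367 × 2.86) = 2.29 points.
- Clustered, t on 11 df: 2.201·√(0.16/3367 × 2.86) = 2.57 points.

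**Step 4: coverage of the unadjusted interval.** With the areas treated as a sample, coverage ≈ 2Φ(1.96/√DE) − 1. The simulation used beta-binomial clusters, 12 per arm, gamma-distributed sizes with CV 0.33, exact limits and 40,000 runs.

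| Case | DE | Formula | Simulation |
|---|---|---|---|
| ICC 0.0025 | 1.77 | 85.9% | 86.4% |
| ICC 0.0060 | 2.86 | 75.3% | 75.9% |
| ICC 0.0095 | 3.95 | 67.6% | 68.3% |
| Printed design effect | 1.95 | 84.0% | – |

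**Step 5: can the arm intervals separate while the clustered comparison is not significant?** Take 673/3367 (20.0%) against 572/3367 (17.0%). The second exact interval is 15.73% to 18.30%, wholly below 18.65%. With DE 2.86 the clustered comparison gives z = 1.87, p = 0.061 (normal) or 0.074 (t, 22 df). So it can happen. Holding the first arm at 20.0% and using the normal comparison, the range of second-arm rates where it happens is:
- DE 2.86: about 16.9% to 17.3%.
- DE 3.95: about 16.3% to 17.3%.
- DE 1.77 or 1.95: none. With t on 22 df at DE 1.95, a sliver of about 0.1 point.

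**The case against.** The strongest objection is about the target. The 75% treats the 12 areas as drawn from a wider population of areas. The document describes 24 areas that make up the study site and says the number available is fixed. For the rate in those particular 12 areas, variation between areas is not sampling error and the interval would not undercover in this way. For the rate across all 24, halving the between-area part gives DE = 1 + 0.5 × 1.86 = 1.93 and coverage of about 84%. The calculation also ignores the restricted allocation, which balanced predicted preterm birth. This stands as a limit on the size: the coverage figure must carry its assumption. It does not rescue the method. The Discussion speaks of population-level rates and of informing policy in other settings, and the sample size section already treats between-area variation as error.

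Second, no test or decision rule uses the arm interval. That also stands. A reader might infer that the trial's main result is invalid, but the effect estimates are assigned to GEE.

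Third, a reader might infer that the arm rates are meant to supply a population estimate of preterm burden. The stated aims do not include that; they concern impact, infection prevalence and test accuracy.

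Fourth, a reader might infer that the arm intervals will generally contradict the clustered comparison. Step 5 shows this only in a narrow range at the central ICC and essentially not at the lower design effects.

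Finally, the exact interval is named only for the preterm rate, and the only ICC given is for that outcome, so no coverage figure can be put on the other outcomes.

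**Conclusion.** The point holds as a flaw in a stated descriptive interval. The prescribed method contradicts the plan's own evidence of clustering for the same outcome, and nothing elsewhere in the article corrects it. With areas read as a sample and the stated ICC and CV, coverage is about 75% in place of 95%, and the half-width is too small by a factor of √2.86 = 1.69 before any small-sample allowance. The size depends on the ICC, but on that reading no value in the stated interval brings coverage above about 86%. The consequence is limited to how precisely the arm rates appear to be known. The primary relative risk and risk difference do not depend on it. It should be corrected because the repair is simple and uses a model already planned.

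**What to change.** In the Analysis section, replace the exact binomial interval for each arm's preterm live birth rate with a cluster-adjusted one. Either of two forms would do:
- the arm-level estimate from the GEE model already planned, with a small-sample correction for 12 areas per arm; or
- an interval from the 12 area proportions in each arm, using t on 11 df.

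Use the same method wherever arm-level rates of other outcomes are given intervals.

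The change is one sentence of text and a line of code. It needs no new data and changes neither sample size nor conduct. The cost is wider reported intervals: at a 20% rate and the central ICC, about ±2.3 to ±2.6 points in place of about ±1.4.

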### Sample size and analysis

In order to calculate the sample size, we first hypothesized that a population-level reduction in the preterm rate in the range of 15–20 % would be of public health importance, given the importance of the outcome and the level of complexity of any future scaled- up programmatic implementation of the intervention. Once we established this desired effect size range, we worked through a series of calculations (with corresponding assumptions) to determine the number of babies required to achieve sufficient power (i.e. 80 %) for a population-level reduction in this range (i.e. 15–20 %).

Given that the intervention is directed only at a subset of the population, we first estimated the proportion of preterm birth among both infected and non-infected women. Estimation of these proportions requires three parameters:The proportion of preterm in the population: we estimated this to be 20 %, based on our prior data from this population [51].The proportion of women in the intervention clusters that actually receive treatment under the universal screening program, or equivalently an estimate of the total proportion of women with UTI and/or AVF (Nugent ≥4).The ratio of preterm birth risk among infected and non-infected women; we estimated this ratio to be 2.5 from the literature.

From previous data and the literature, we estimated that about 15 % of women in this setting have either AVF, UTI, or both. Among those with AVF, some will fall into the intermediate flora score range (Nugent score 4–6) and some into the BV scoring range (Nugent score 7–10). Our best estimates of the relative proportions in these two subgroups was approximately 85 % within the BV (Nugent 7–10) range, with the remaining 15 % of women with AVF falling within the intermediate flora scoring range (Nugent 4–6) [24]. We based our prevalence estimates and treatment effect size on prior studies of similar screening and treatment programs for **all abnormal vaginal flora** (Nugent scores ≥4).

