### Data safety and monitoring board and interim analysis

An independent Data Safety Monitoring Board (DSMB) consisting of a clinical trialist and infectious disease specialist, an obstetrician-gynecologist and a biostatistician is established for this trial. The DSMB met prior to the start of data collection to review and approve the study protocol, and met in person to review interim analysis after 33 % and 66 % of the study outcomes were achieved. At both meetings (February 2014, February 2015), the DSMB indicated the study should continue as planned. The DSMB reviewed the data collected in the study for evidence of issues related to safety of study subjects and the efficacy of the study interventions. The DSMB may also request further meetings, either face-to-face or by teleconference. At all meetings, minutes are kept of the deliberations of the DSMB and provided to the JHU Insitutional Review Board (IRB), the Ethical Review Committee of the International Centre for Diarrhoeal Diseases Research, Bangladesh, and Brigham and Women’s Hospital.

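### GEE standard errors on 24 clusters, with no small-sample method named and no allowance for the restricted randomisation, do not secure the stated 5% Type I error in either direction

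*Protocol article*

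**What the plan says.** The Sample size and analysis section starts from a fixed 24 clusters ("As the number of clusters available is fixed") and gives the live births needed per arm to detect an 18.4% "relative reduction with 80 % power and allowing 5 % Type I error is approximately 3367". It reports an intra-cluster correlation of 0.0060 (95% CI 0.0025 to 0.0095) and a coefficient of variation of cluster size of 0.33.

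The Randomization section allocates 12 clusters to each arm. From 2,704,156 possible allocations it kept 164. These have between-arm ratios of predicted preterm births and predicted total births within 0.975 to 1.025, and an even split of the 13 areas from an earlier birth-spacing study.

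The Analysis section uses log-link and identity-link binomial regression for the primary outcome and then states: "The standard error of this estimate will be constructed using generalized estimating equations and a 95 % confidence interval calculated". It closes by promising, for all estimates of impact, "confidence intervals constructed from standard error estimates adjusted for the cluster randomization using GEE". Models are first presented unadjusted. A second set adjusts only for variables found to be imbalanced.

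**The concern.** Two features of the design bear on whether a GEE interval has its nominal coverage here, and the stated method addresses neither.

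First, the usual GEE (sandwich) variance is biased low when clusters are few, and a normal quantile is too small for a variance estimated from 24 clusters. Both make the interval too narrow.

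Second, the allocation was restricted on past values of the primary outcome. If cluster risks persist over time, chance differences between arms are smaller than the between-cluster variation implies. An analysis that ignores the restriction is then conservative. The stated rule for covariate adjustment would not pick up the balancing variables, because the allocation made them balanced.

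The primary test could thus lie above or below the 5% used for the sample size, and the reader of the trial report could not tell which.

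**Working it through.** **1. Inputs from the protocol article.** 24 clusters, 12 per arm (Randomization). Preterm proportion 0.20 ("we estimated this to be 20 %, based on our prior data from this population"), relative reduction 18.4%, intra-cluster correlation ρ = 0.0060, cluster-size variation γ = 0.33, power 80%, Type I error 5%, 3367 live births per arm (Sample size and analysis).

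**2. The plan's own figure.** The intervention proportion is 0.20 × (1 − 0.184) = 0.1632, and the mean of the two proportions is 0.1816. With two-sided normal quantiles:

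n = [1.96 √(2 × 0.1816 × 0.8184) + 0.8416 √(0.20 × 0.80 + 0.1632 × 0.8368)]² / 0.0368² = 1722 per arm.

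Mean cluster size at this stage is θ = 2 × 1722 / 24 = 143.5. The article's formula gives 1 + 0.006 × (143.5 − 1 + 143.5 × 0.33²) = 1.949, against 1.95 stated. Then 1722 × 1.949 = 3356 per arm, against 3367 (0.3% apart), and 2 × 3367 / (0.9 × 0.9) = 8314, as stated. The figure reproduces with a two-sided 5% test and normal quantiles. This confirms the inputs; it does not assess the design-effect formula.

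**3. Simple approximation for the default interval.** With equal clusters, the uncorrected sandwich variance is too small by a factor of about 11/12 within each 12-cluster arm.
- Normal quantile only: 2 × P(t₂₂ > 1.96) = 6.3%.
- With the variance bias: 2 × P(t₂₂ > 1.96 × √(11/12)) = 2 × P(t₂₂ > 1.877) = 7.4%.

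**4. Simulation under simple randomisation.** Null trials with 12 + 12 beta-binomial clusters, mean size 3367 / 12 = 281, γ = 0.33, ρ = 0.006, risk 20%, log link, independence working correlation:
- plain sandwich with 1.96: 7.8% to 8.0% in independent runs; 7.9% and 8.0% at the two ends of the interval for ρ; 8.9% if γ were 0.6;
- plain sandwich with t₂₂: 6.3% to 6.5%;
- Kauermann-Carroll correction with t₂₂: 5.2% to 5.4%;
- cluster-level t test: 4.9%.

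**5. Simulation under the restricted randomisation.** The article does not say how strongly cluster risk in the earlier data predicts risk in the trial, so this correlation (persistence) is an assumption and is varied. Earlier births per cluster are also assumed. If all of the roughly 16,000 births came from these clusters, the figure is 16,000 / 24 = 667. From the stated population and birth rate over 15 months it is 100,000 × 0.027 × 1.25 / 24 = 141. Type I error of the plain sandwich with 1.96, unadjusted:

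| Earlier births per cluster | 0 | 0.3 | 0.5 | 0.7 | 0.9 |
|---|---|---|---|---|---|
| 667, first run | 8.1% | 6.6% | 5.6% | 4.4% | 3.0% |
| 667, second run | 8.0% | – | 6.1% | 4.8% | 2.7% |
| 141 | 8.0% | – | 6.5% | 6.1% | 4.6% |

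The columns are the assumed persistence. The first run used 8000 trials per cell, so its Monte Carlo standard error near 8% is √(0.08 × 0.92 / 8000) = 0.3 percentage points.

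**6. Candidate remedies under the restriction.** Kauermann-Carroll with t₂₂ and no adjustment becomes conservative, at about 4% down to 1.5%. A cluster-level analysis adjusted for the earlier preterm rate stayed between 4.4% and 5.4% in every case.

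**The case against.** The strongest reply is that the missing correction is inferred from silence. The article does not say uncorrected, sandwich, or normal reference. A separate statistical analysis plan, not shown here, may name a correction and a t reference, and a journal article may properly leave such detail to it. This stands as a limit on the claim: the 8% is the error of the default method, and the article does not establish that the default will be used. The point survives because the article does fix the method. It names GEE for the primary outcome, repeats it for all impact estimates as the adjustment for cluster randomisation, and sets an adjustment rule that passes over the balancing variables.

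The second reply is that the restriction protects the primary test. It may. A reader might infer from the 8% that every interval is too narrow and that the primary error exceeds 5%. The documents do not support that, because with strong persistence the plain interval is at or below 5%. Equally, nothing in the article shows that cluster risks persisted from the 2007–2008 data to a trial with interim reviews in 2014 and 2015. The offset therefore cannot be relied on as validation.

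**Conclusion.** The point holds in limited form. The stated method does not secure the 5% Type I error on which the trial was sized. The default GEE interval gives about 8% under simple randomisation. Under the actual allocation, the unadjusted primary test runs from about 8% down to 3% as persistence goes from 0 to 0.9. The direction of the error is not known from the documents. For secondary outcomes such as sepsis, stillbirth and mortality any offset is less certain, because the balancing used only predicted preterm births and total births.

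These figures rest on the protocol's correlation, cluster-size variation and sample size, on an independence working correlation, and on assumed values for persistence and for earlier births per cluster.

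A reader might also infer that the two interim reviews inflate the error. The article says "Interim (i.e. for DSMB analyses) and final analyses will follow the same protocol" and that the board "met in person to review interim analysis after 33 % and 66 % of the study outcomes were achieved", with efficacy among the matters reviewed. But nothing makes a 95% interval excluding no effect a stopping rule. Both reviews ended in continuation, and any boundary may sit in a charter or analysis plan not shown. Looking at the data without the option of an efficacy stop does not inflate the final test. The documents do not support that inference, and they give no ground for lowering the final significance level.

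**What to change.** **Primary outcome.** Specify one of the following before the final analysis:
- a cluster-level regression, or GEE with a Kauermann-Carroll or Fay-Graubard corrected sandwich, adjusted for the balancing variables (earlier cluster preterm rate and births), with t quantiles on 24 minus the number of cluster-level parameters: 24 − 2 = 22 unadjusted, 24 − 4 = 20 with both balancing variables; or
- a permutation test over the 164 eligible allocations, which reflects the restriction directly. The set is large enough for a 5% test, since 8 / 164 = 4.9%.

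**Secondary outcomes.** Use the same small-sample correction and t reference.

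**Interim reviews.** At most, report whatever efficacy boundary was in force at the two reviews.

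**Cost.** No new data are needed beyond the earlier cluster data and the list of eligible allocations used at randomisation. Where the offset is weak, intervals widen. For equal clusters and no adjustment, the factor is about (2.074 / 1.96) × √(12/11) = 1.058 × 1.044 = 1.10. Adjustment uses one or two further degrees of freedom, and where persistence is strong it recovers precision that the unadjusted analysis gives up.

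### Allocation was tightly restricted on predicted preterm birth, but the planned models leave that factor out and choose adjustment variables by observed imbalance

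*Protocol article*

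**What the plan says.** Protocol article, Randomization: "The units of randomization in this trial are the 24 CHW areas, each comprising several adjacent villages". Eligible allocations were those where "intervention vs. control ratios of predicted preterm birth and predicted total births were within 0.975 to 1.025". In addition, the 13 areas from an earlier birth-spacing study "were allocated equally to intervention and control (i.e. 6 and 7 or 7 and 6"). The result: "Among the 2,704,156 sequences, 164 sequences met the criteria, from which a single sequence was randomly selected".

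Protocol article, Analysis: the relative risk and risk difference come from binomial regression with GEE standard errors. On adjustment, the section says: "These models will be presented without adjustment, and a second set of analyses will be conducted with adjustment for any variables". The clause on the second set reads in full: "a second set of analyses will be conducted with adjustment for any variables found to be imbalanced between the groups (if necessary"). The characteristics named for the comparability check are maternal, paternal, household and socio-economic. No restriction factor is named for any model, and the test is not referred to the set of eligible sequences. The same section says that interim and final analyses follow one protocol.

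**The concern.** Restriction removes chance differences between the arms in the factors it balances. If the prior cluster preterm rate predicts the trial-period rate, the estimate's true sampling variance falls. A model without that factor still counts the associated between-cluster variation in its standard error.

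The second set of models does not repair this. A rule that adds a covariate only when it looks imbalanced will normally leave out variables that the design forced to balance. It also makes the content of the adjusted model depend on the observed data, and that holds whatever the prior rate predicts.

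At stake are the calibration of the main test, some power, and a covariate set that can be settled only after the data are seen. The article states a rule here, so this is more than a detail left to an analysis plan.

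**Working it through.** **Inputs (Protocol article).** From Sample size and analysis: control rate 0.20; relative reduction 18.4 %, so 0.1632 under intervention; 80 % power; 5 % Type I error (taken as two-sided); ICC 0.0060; coefficient of variation of cluster size 0.33; 3367 live births per arm. From Randomization: 24 clusters, 12 per arm, and the three restrictions. **Assumed:** r, the correlation between a cluster's prior preterm rate and its trial-period rate, varied from 0 to 0.9.

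**1. The article's own figures reproduce.** Under individual randomisation, n = 1722 per arm, so the mean cluster size is 2 × 1722 / 24 = 143.5. Design effect = 1 + 0.006 × (143.5 − 1 + 143.5 × 0.33²) = 1.949. Then 1722 × 1.95 = 3358, against 3367 stated, and 2 × 3367 / (0.9 × 0.9) = 8314.

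**2. Tightness of the restriction.** 164 / 2,704,156 = 0.0061 %.

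**3. Hand bound on the gain.** At the planned size, 3367 / 12 = 280.6 births per cluster, the design effect is 1 + 0.006 × (279.6 + 280.6 × 0.33²) = 2.861, and power with a normal reference is about 0.64. Suppose adjustment for the prior rate removed a share r² of the between-cluster part at no cost. The design effect would be 1 + 1.861 × (1 − r²): 2.69 at r=0.3, 2.40 at r=0.5 and 1.95 at r=0.7. Power would be 0.67, 0.72 and 0.80. This is an upper bound, because it treats the variance as known.

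**4. Simulation.** 2500 trials per setting; 24 clusters; the inputs above; allocation drawn under the three restrictions; log-link model with cluster-robust errors. *Corrected* means a leverage-corrected standard error with a t reference. *Uncorrected* means the ordinary sandwich with a normal reference.

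Unadjusted model under no effect:

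| r | true SD of log RR | mean SE, uncorrected | mean SE, corrected | Type I error, uncorrected | Type I error, corrected |
|---|---|---|---|---|---|
| 0 | 0.082 | 0.077 | 0.085 | 0.078 | 0.043 |
| 0.3 | 0.081 | 0.077 | 0.085 | 0.078 | 0.035 |
| 0.5 | 0.077 | 0.077 | 0.086 | 0.054 | 0.029 |
| 0.7 | 0.072 | 0.078 | 0.086 | 0.043 | 0.020 |
| 0.9 | 0.064 | 0.078 | 0.086 | 0.022 | 0.009 |

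Power for the 18.4 % reduction, corrected:

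| r | unadjusted | prior preterm rate | all three factors |
|---|---|---|---|
| 0 | 0.60 | 0.57 | 0.53 |
| 0.3 | 0.59 | 0.59 | 0.53 |
| 0.5 | 0.60 | 0.63 | 0.58 |
| 0.7 | 0.60 | 0.70 | 0.66 |
| 0.9 | 0.60 | 0.80 | 0.75 |

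The Monte Carlo standard error is about 1 point for power: √(0.6 × 0.4 / 2500) = 0.0098.

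**5. Reading.** The true SD falls as r rises while the unadjusted standard error does not move, which is the mismatch. Adjustment needs the correction as well: adjusted for prior rate with uncorrected errors, Type I error was 0.084 to 0.089 across r. Corrected, it was 0.032 to 0.039.

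**Limit.** About 2.3 % of simulated allocations met the criteria, against 0.0061 % in the article. The real restriction was therefore tighter than the simulated one, and the sizes are indicative.

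**The case against.** A reader might infer that the planned intervals are simply too wide. The article does not support that. It names GEE errors with no small-sample correction, and with 24 clusters the ordinary sandwich is too small. At r=0 its Type I error is 0.078, above nominal; at r=0.5 and 0.7 the two errors roughly cancel (0.054 and 0.043). A separate simulation of 3,000 trials per setting agreed: 0.060, 0.053 and 0.040 uncorrected at correlations of 0.6, 0.7 and 0.8 (with 150, 300 and 667 prior births per cluster), against 0.040, 0.033 and 0.026 corrected. This objection stands, though two errors that cancel by an unknown amount are no reason to keep both.

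A reader might also infer that power is certainly wasted. That needs r, which appears nowhere. Choosing preterm status as a restriction factor suggests that the investigators thought it predictive, but gives no figure. At r of 0.3 or below there is nothing to gain.

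Nor does it follow that all three factors belong in the main model. Relative to no adjustment, that lost about 1 to 8 points at r of 0.5 or below. The cost depends on method: under a milder leverage correction it was only 0.5 to 1.5 points relative to prior rate alone.

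Leaving out balanced factors does not itself inflate Type I error, so on this ground the unadjusted analysis is not invalid. The unadjusted and adjusted analyses are two separate sets. The baseline power near 0.60 to 0.64 comes from applying the design effect at the smaller cluster size, a separate matter.

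**Conclusion.** The mismatch between design and analysis holds on the text: allocation was restricted on three factors, no planned model is said to contain them, and the stated covariate rule is data-driven and would normally skip them. That part needs no assumption.

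Its size is conditional. With corrected errors, the unadjusted test is conservative once the prior rate is moderately predictive (Type I error about 0.029 at r=0.5 and 0.020 at r=0.7). Adjusting for that rate gains about 3 and 10 power points there, nothing at r=0.3, and costs about 3 points at r=0. With uncorrected errors and a normal reference, the conservatism is partly or fully offset. A definite loss of power, or intervals that are definitely too wide, cannot be claimed from this document. The change is worth making; it is an improvement in efficiency and prespecification, and does not rescue an invalid test.

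**What to change.** Before the final unblinded analysis:

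- Prespecify a model adjusted for the cluster-level prior preterm rate, using small-sample-corrected GEE or cluster-level regression with a t reference. A permutation test over the 164 eligible sequences can stand beside it or replace it; its smallest two-sided p is about 2/164 = 0.012.
- Replace the imbalance-triggered rule with a fixed, prespecified covariate list.
- Keep the unadjusted estimate as supportive, and treat adjustment for all three restriction factors as a sensitivity analysis.

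**Cost.** The prior data were already used to randomise, so nothing new is collected. The model spends one cluster-level degree of freedom and loses a little power if the prior rate does not predict. A documented amendment is needed: the Analysis section commits interim and final analyses to the same protocol, and the section on the monitoring board reports that both interim reviews (February 2014 and February 2015), which covered efficacy, have taken place.
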